### Data collection

An overview of the content of the different data collection methods can be found in Fig. 3.

**Fig. 3 Fig3:**
[figure not shown]
Content of data collection in ‘Patients in cohort’: patients participating in the prospective cohort design; ‘Patients in stepped-wedge based control period: data collection for patients participating in the control group of the stepped-wedge based design; ‘Patients in stepped-wedge NPRL2.0; data collection for patients participating in the intervention group of the stepped-wedge design

Patients participating in NPRL2.0 are asked to fill in four questionnaires electronically or on paper: T1 after initial contact with healthcare professionals about their CMP complaints (50 min completion time); T2 3 months after T1 (30 min completion time); T3 6 months after T1 (30 min completion time); and T4 9 months after T1 (50 min completion time).

Additionally, assessment tool 1 will be used for research purposes, as well as for decision-making in primary care. Therefore, patients in the control group will complete assessment tool 1 as part of the questionnaire at T1. Patients in the intervention group will complete it during their consultations in primary care. Assessment tool 1 will assess the level of complexity of the pain complaints and consists of one Visual Analogue Scale (VAS) for pain intensity and nine dichotomous questions on biopsychosocial factors.

At the end of the study, records of the treatment characteristics of each patient will be collected from the participating practices and rehabilitation centers.

In order to encourage completion of the questionnaires, patients will be reminded up to three times by phone if they have not responded within one week. If incomplete questionnaires are returned, patients will be contacted by phone to answer the remaining questions. The researcher who performs the analyses will be blinded as to patient allocation.

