**Methods:**

In this pragmatic study, it is expected that two local networks with 105 patients will participate in the prospective cohort study and six local networks with 184 patients in the stepped-wedge based design. Healthcare professionals in the local networks will recruit patients. Inclusion criteria: age ≥ 18 years; having CMP; willing to improve functioning despite pain; and adequate Dutch literacy. Exclusion criteria: pregnancy; and having a treatable medical or psychiatric disease. Patients will complete questionnaires at baseline (T1), 3 months (T2), 6 months (T3), and 9 months (T4). Questionnaires at T1 and T4 will include the Pain Disability Index and Short Form Health Survey. Questionnaires at T1, T2, T3, and T4 will include the EQ-5D-5L, and iMTA Medical Consumption and Productivity Cost Questionnaires. Outcomes will be compared using linear mixed-model analysis and costs will be compared using bootstrapping methods.

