### Intervention

NPRL2.0 is an integrated, transmural healthcare network for patients with CMP, focusing on improving the level of functioning of patients, despite pain. In the primary care of NPRL2.0, the GP is the gatekeeper for assessing the level of complexity of pain complaints, referral, and treatment selection. In the Netherlands, therapists (such as physiotherapists, practice therapists, and occupational therapists) in primary care can be visited by people with CMP directly, without referral. Therefore, therapists will also be able to assess the level of complexity of the pain complaints and to advise these patients to visit a GP if necessary. Depending on the level of complexity involved, the follow-up policy will either include advice without further treatment, monodisciplinary treatment in primary care, interdisciplinary treatment in primary care (collaboration between GPs, primary care therapists, and mental health practice nurses in assessing and treating patients with CMP who need mental support besides physical exercise) or interdisciplinary treatment in secondary or tertiary care (Fig. 2). Primary care in NPRL2.0 consists of the following elements:

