### Recruitment of patients

Patients with CMP complaints, who visit the participating GPs and therapists via direct access, will be informed about the study and asked for consent to transfer their contact details to the research team. The research team will contact these patients by phone to inform them about the study and ask for oral consent for participation. Subsequently, the patients will receive the first questionnaire (T1) electronically or by post, in which they can give electronic/written informed consent for participation in the study.

Patients will be eligible if they are ≥ 18 years at the start of the study, have CMP or musculoskeletal pain with a high risk of becoming chronic, are willing to improve their functioning despite the pain, and have adequate Dutch literacy to complete the questionnaires. Exclusion criteria are pregnancy or any medical (orthopedic, rheumatic or neurological) or psychiatric disease which could be treated by a more appropriate therapy, according to the expert opinion of the GP. The data will be handled based on intention-to-treat.

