### Data analysis

Demographic data (e.g. gender, age, home situation, level of education, nationality, and co-morbidities) will be described overall and separately for the intervention and control groups. Frequencies are to be presented for categorical variables, means and standard deviations (SDs) for normally-distributed continuous variables, and medians and ranges for non-normally-distributed continuous data. The two groups will be tested on differences between characteristics, using the *t*-test for continuous variables and the chi-squared test for categorical variables. If variables differ between the two groups, with *p* ≤ 0.10, they are considered to be potential confounders in further analyses.

Outcomes on questionnaires will be compared using linear mixed-model analysis, to take into account repeated measurements in patients as well as the effects of the clustering of patients within local networks. The fixed part of the model contains treatment group (intervention/control), time, treatment group*time, and cluster (local network). To assess the learning effect in local practices, the time (months) that a local network participates in NPRL2.0 will also be taken into account as a fixed variable. Variables known to be related to the outcome and differing between treatment groups at T1 (*p* ≤ 0.10) will be added to the model. An unstructured covariance structure will be used for repeated measures. Missing values for items in the questionnaires will be handled according to the scoring algorithms of the questionnaires. Missing variables in the follow-up data will not be imputed because linear mixed-model analysis is a flexible method for handling missing data for stepped-wedge and repeated-measures designs (likelihood-based approach). Linear mixed-model analyses will be performed using IBM SPSS Statistics for Windows (version 24.0 or higher, Armonk, NY: IBM Corp.) according to the intention-to-treat principle. Other missing values for non-repeated measures will be handled by multiple imputation, which means that missing values will be predicted using existing values for other variables [66].

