## Discussion

The Network Pain Rehabilitation Limburg 2.0 (NPRL2.0) has been developed in order to provide integrated care with a biopsychosocial approach for people with CMP with the goal of improving their level of functioning. Moreover, it is intended to accomplish the Quadruple Aim: improvement of pain-related disability of people with CMP; improvement of experiences of care of people with CMP; improvement in the meaning of work for healthcare professionals; and the reduction of healthcare costs of people with CMP. In this quantitative study, the effectiveness of NPRL2.0 in reducing the pain-related disability of people with CMP will be assessed. In addition, the influence of NPRL2.0 on healthcare costs will be examined with a cost-effectiveness and cost-utility analysis. Moreover, the learning curve of healthcare professionals working in NPRL2.0 will also be studied.

NPRL2.0 is a multidimensional, complex intervention, executed in daily practice [33]. Because of the practice-based approach of this study, a randomized controlled trial design (RCT) is not suitable. Therefore, a pragmatic study with stepped-wedge based design using randomization of the local networks was seen as a viable alternative to an RCT [70]. The local primary care networks involved would be randomly assigned to the three steps (A, B or C) in order to randomize the duration of being a control group or intervention group. Local networks are their own controls in a stepped-wedge based design. Healthcare professionals are instructed to recruit patients at their first consultation for CMP complaints. Therefore, it is expected that patients with comparable complexities of complaints will be distributed equally over the control and intervention groups. Moreover, in this practice-based research, connections between science, policy, and practice exist during implementation and execution of NPRL2.0, leading to evidence-based practice. The external validity of the results of such as this pragmatic study of NPRL2.0 is commonly higher than that of RCTs because the results are more generalizable.

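### T1 is called baseline but follows the first professional contact and is not required to precede treatment, so the T1-to-T4 contrast may lose any early effect

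*Protocol article*

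**What the plan says.** The Abstract (Methods) labels T1 as baseline: "Patients will complete questionnaires at baseline (T1), 3 months (T2), 6 months (T3), and 9 months (T4". The Baseline characteristics section likewise collects its variables at T1.

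The Data collection section (text under Fig. 3) defines the time point differently: "T1 after initial contact with healthcare professionals about their CMP complaints". The later questionnaires are timed from T1.

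The order of events comes from three sections:
- Discussion: "Healthcare professionals are instructed to recruit patients at their first consultation for CMP complaints".
- Recruitment of patients: contact details pass to the research team, then "The research team will contact these patients by phone to inform them about the study". After that, "Subsequently, the patients will receive the first questionnaire (T1) electronically or by post".
- Data collection: "patients will be reminded up to three times by phone if they have not responded within one week".

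Under Intervention, in NPRL2.0 primary care "the GP is the gatekeeper for assessing the level of complexity of pain complaints, referral, and treatment selection". Data collection adds that intervention patients complete the assessment tool during consultations, whereas controls complete it inside the T1 questionnaire.

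The Data analysis section models group, time, group-by-time and local network. It also adds covariates chosen at the same time point: "Variables known to be related to the outcome and differing between treatment groups at T1" (p ≤ 0.10).

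**The concern.** A baseline should be measured before the exposure under study can act. Here T1 always comes after the first contact, by an interval that varies between patients and has no stated upper limit. In the intervention period that contact takes place with a professional working under NPRL2.0. The article neither states that treatment has begun by T1 nor prevents it.

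Two parts of the analysis depend on T1 being untouched by care. The group-by-time term compares later outcomes with T1. The covariate rule treats a group difference at T1 as potential confounding. If the first contact, or sessions soon after it, changed a T1 health score differently in the two groups, the first would subtract part of the effect and the second could adjust part of it away. The direction is toward no difference. This matters because the Discussion hypothesises that outcomes will be no worse than under usual care, although the stated research aims are improvements over usual care.

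**Working it through.** The document gives no figure to reproduce. It states no delay to T1, no speed of onset and no early effect, so the sizes below are illustrations.

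**1. What the model estimates.** Let D1 and D4 be the group differences (NPRL2.0 minus control) at T1 and T4. The Abstract places the PDI and SF-12 at T1 and T4 only. With group, time and group-by-time in the model:
- group-by-time at T4 = D4 − D1
- group difference at T4 = group + group-by-time = D1 + (D4 − D1) = D4

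If a share f of the T4 effect is already present at T1, D1 = f × D4. The interaction then equals (1 − f) × D4, while the T4 difference remains D4.

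**2. Size for assumed f.** Power of the interaction, if it were 80% at f = 0 with two-sided alpha 0.05, is Φ[(1 − f)(1.960 + 0.842) − 1.960]. At f = 0.20: 0.80 × 2.802 − 1.960 = 0.281, and Φ(0.281) = 0.61. The last column scales 13 PDI points, the minimal important change given under Health assessment.

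| f (assumed) | Effect kept | Power | 13 PDI points appear as |
|---|---|---|---|
| 0% | 100% | 80% | 13.0 |
| 5% | 95% | 76% | 12.4 |
| 10% | 90% | 71% | 11.7 |
| 20% | 80% | 61% | 10.4 |
| 30% | 70% | 50% | 9.1 |

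The 80% starting point is itself an assumption for the PDI, because the Sample size section powers the trial on the EQ-5D-5L.

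**3. From delay to f.** If the effect rose linearly from the first consultation to a plateau after P weeks, reached before T4, then f = d/P for a T1 delay of d weeks. With d = 1 to 5, f runs from 1/13 = 8% to 5/13 = 38% for P = 13, and from 1/26 = 4% to 5/26 = 19% for P = 26. Both d and P are assumed, and a rise starting on the day of an assessment contact is close to a worst case.

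**4. Adjusting for an affected T1 score.** With equal SDs and a T1–T4 correlation r, the T4 difference adjusted for T1 is D4 − r × D1 = D4(1 − r × f). For an assumed D4 = −5, r = 0.6 and f = 0.20 this is −5 × 0.88 = −4.4. A simulation with 400,000 patients per group and SD 13 agreed:

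| f | T4 difference | Change from T1 | T4 adjusted for T1 |
|---|---|---|---|
| 0% | −5.0 | −5.0 | −5.0 |
| 10% | −5.0 | −4.5 | −4.7 |
| 20% | −5.0 | −4.0 | −4.4 |
| 30% | −5.0 | −3.5 | −4.1 |

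The loss is greatest for the contrast against T1, smaller when a T1 score is a covariate, and absent from the unadjusted T4 difference.

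**The case against.** The strongest reply is that T1 has to follow first contact. Patients are identified at the consultation and consent within the T1 questionnaire, in both groups alike. A journal article may leave completion windows to the full protocol, and Fig. 3 is not shown. The Discussion expects no short-term benefit, so D1 may be near zero. D4 can be estimated from the planned model.

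Much of this stands. Some contact before T1 is unavoidable, the loss is nil without an early effect, and D4 is robust to the problem. What remains is that the article itself states when T1 is taken, and that rule allows T1 to fall after treatment has started. The no-short-term-benefit remark rests mainly on the time professionals need to adopt the approach, not on weeks since a patient's own consultation, so it does not show that D1 is zero.

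A reader might infer several stronger things that the document does not support:
- **That NPRL2.0 care has already begun at T1.** The text says only that T1 follows initial contact. It does not say that treatment sessions or eHealth modules have started.
- **That the first consultation falls outside the costs.** Cost assessment takes consultations and treatment hours from patient records in both groups and states no start at T1.
- **That the QALY period should start at the first consultation.** No EQ-5D-5L is taken then, so this would need extrapolation.
- **That T1 health scores will be used as covariates.** The rule does not name them. It does not exclude them either, but the characteristics listed just before it are demographics and co-morbidities, most of which care cannot change.

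**Conclusion.** The point holds as a conditional one. T1 is treated as a baseline but is not tied to a point before NPRL2.0 exposure. For the PDI and SF-12, the group-by-time term is therefore a contrast against a measurement that may follow the start of care. If a share f of the T4 effect has accrued by T1, that term is reduced by the same share. The document does not allow f to be derived, and it may be zero. The 5% to 30% range and the delay scenarios above are assumptions, not estimates of bias in this trial.

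The unadjusted T4 difference keeps the effect, but it does not correct for a genuine imbalance between patients recruited in the two periods. Neither estimate is sufficient alone, since a T1 difference caused by early care cannot be told apart from one caused by selection unless the dates are known. This calls for a low-cost improvement. It does not show that the results would be invalid.

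**What to change.** 1. **Recruitment of patients and Data collection:** require T1 to be completed within a fixed window of the first consultation and before the first treatment session, in both groups. This governs the timing of the questionnaire and is no reason to hold back care. Questionnaires that miss the window are flagged. Because T1 would still follow the first consultation, the window limits the problem without removing it.
2. **Dates:** record the first consultation, the first treatment session and T1 for each patient, and count sessions before T1 from the treatment records already due to be collected.
3. **Data analysis:** keep all patients in the main analysis and report the T4 group difference alongside the group-by-time term.
4. **Sensitivity analysis:** repeat the analysis without patients whose T1 came after treatment started. This stays secondary, because those patients may differ from the rest.
5. **Covariates:** flag any T1 health score selected under the p ≤ 0.10 rule as possibly affected by first contact, and show results with and without it. Banning such scores outright would give up adjustment for real differences in who is recruited by professionals who know the period.

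The cost is three dates per patient, a count from records already planned, a few sentences of protocol text and one extra analysis. The downside is that some T1 questionnaires will miss the window and have to be flagged.

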### Outcome measures

#### Baseline characteristics

Baseline characteristics will be collected at T1 and they will include questions about: birth date, gender, nationality, marital status, family composition, level of education, and co-morbidities.

#### Health assessment

The Pain Disability Index (PDI) will be used as the primary outcome for pain-related disability. It measures the influence of pain on a patient’s life and on the performance of daily activities. The questionnaire consists of seven items that measure the complexity of the disabilities experienced in different situations such as work, leisure time, activities in daily life, and sport. Each item is scored on a scale from 0 (no disability) to 10 (severe disability). Scores from the individual items are summed to a total (0–70). The minimal important change is 13 points for patients with CMP [41]. The Dutch version of the PDI has proven internal consistency and test–retest reliability [42].

The Dutch language version of the Short Form Health Survey (SF-12) will be used as the primary outcome for cost-effectiveness, measuring quality of life on specific domains. The SF-12 has proven to be a practical, reliable, and valid instrument for use in both general population surveys and in studies of chronic disease populations in the Netherlands [43, 44]. The SF-12 will be summarized into two scales: a physical component score (PCS) and a mental component score (MCS), in accordance with the guidelines for the SF12 instrument [45]. The PCS comprises the domains of physical functioning, physical role limitation, bodily pain, and general health perceptions. The MCS comprises the domains of vitality, social functioning, emotional role limitations, and general mental health. Both scores range from 0 to 100 (a higher score indicates a better quality of life) with a minimal clinically important difference of 8.9 for low back pain [46]. These sub-scales will be used in the effectiveness analysis. Besides the SF-12 score, the Short-Form Health Survey with six dimensions (SF-6D) scores will be used in a sensitivity analysis.

The EQ-5D-5L will be used for the cost-utility analysis: it provides a single health index based on self-reported mobility, self-care, usual activities, pain/discomfort, and anxiety/depression, with a minimal clinically important change of 0.04 [47]. There are five levels in each dimension from which respondents select that which most closely matches their health state. The levels are no, slight, moderate, severe, and extreme problems, coded 1 to 5. A health state index score, ranging from − 0.446 to 1 (worst to best imaginable health status), will be calculated from individual health profiles, using the Dutch utility tariff [48]. QALYs were calculated from utilities by using the area under the curve method. The accompanying visual analogue scale (VAS: 0–100) rates the current health state, with higher scores indicative of better experienced health. The minimal clinically important difference for low back pain is 22.5 [46]. The Dutch version of the EQ-5D-5L was found valid and reliable [49, 50].

The Numeric Rating Scale (NRS) will be used to measure pain intensity on an 11-point scale varying from 0 (no pain) to 10 (worst pain imaginable). At each measurement point (T1-4), the patient will complete the NRS three times: current pain intensity; lowest pain intensity in the last week; highest pain intensity in the last week. The NRS has shown high test–retest reliability and validity [51]. A reduction of 2 points, or 30%, on the pain NRS scores can be seen as clinically important [52].

The Hospital Anxiety and Depression Scale (HADS) consists of 14 items of which seven are related to anxiety and seven to depression. The patient is asked to rate the items on a 4-point scale ranging from 0 (not at all) to 3 (most of the time). Total scores range from 0 to 21 on each subscale: a higher score reflects higher distress. The HADS has a sensitivity and specificity of about 80% and a predictive validity for identification of about 70% [53]. The reliability ranges from 0.84 to 0.96 [54].

The six-item short form Pain Catastrophizing Scale (PCS-6) comprises six definitions of thoughts and feelings when experiencing pain [55]. The patient is asked to rate the definitions on a 5-point scale, ranging from 0 (not at all) to 4 (all the time), with total scores ranging from 0 to 24 [55]. The six-item version is used because it places a lower burden on patients than the original PCS. This form is adequate for detecting pre- to post-treatment changes in pain catastrophizing [56]. The PCS-6 is highly comparable to the original PCS and meets the construct validity criteria. Internal consistency and test–retest reliability of the original PCS appears to be adequate [55–57].

The Pain Self-Efficacy Questionnaire (PSEQ) is used to measure pain self-efficacy [58]. In patients with CMP, it shows satisfactory internal consistency and construct validity [59]. The four-item short form PSEQ-4 (items 4, 6, 8 and 9) will be used because it places a lower burden on patients than the original PSEQ [55]. Items are rated on a 7-point Likert scale ranging from 0 (not at all confident) to 6 (completely confident). The scores are summed, ranging from 0 to 24: the minimal important change is 1.5 points [60]. The PSEQ-4 is a good alternative for the PSEQ as the sensitivity and specificity of the PSEQ-4 are 0.803 and 0.687 respectively, compared with 0.648 and 0.875 respectively for the PSEQ [60].

